#### **4.3.7 Healthcare Utilization**

From Day 2 onwards, patient-assessed measures of healthcare utilization will be performed every morning upon waking until the end of the study (Intake Period plus Follow-up Period) (Table 1).

Measures will include:

- Prescription Medication Use – recorded as reason, type, dose and frequency
- Over-the-counter Medication Use – recorded as reason, type, dose and frequency
- Supplement Use – recorded as reason, type, dose and frequency
- Emergency room or Urgent Care visit – Rated as Y/N; if Y then reason will be recorded
- Medical provider visit – Rated as Y/N; if Y then reason as well as if this is a visit for a co-existing condition (mental health visit, physical therapy, etc.) will be recorded;
- Hospital stay – Rated as Y/N; if Y then reason will be recorded

### 4.3.8 Patient-assessed Bedrest Time

Patients will be asked to estimate the total amount of time (in hours) of bedrest each day. For the purposes of this protocol, bedrest is defined as all rest including resting on the couch or recliner.

Patients will begin self-assessing total daily bedrest (in hours) at the time they provide consent, each morning upon waking in a reflective manner (reflecting back over the cumulative time of bedrest from the previous day).

Following randomization, patients will self-assess total daily bedrest in a reflective manner (reflecting back over the previous day) the total amount of their bedrest time in hours and according to the SOA (Table 1).

### 4.3.9 Laboratory and Inflammatory Biomarkers

If feasible blood samples for hematology, clinical chemistries, and serological measures of immunity, and nasal/oropharyngeal swabs for quantitative viral load assessments (research purposes only) will be collected (see Table 1 and Table 2). Samples collection may occur at the patient's home by a healthcare professional, remotely, or at the study site or clinic. Sampling will be in accordance with acceptable laboratory procedures; additional analyte values may also be reported, consistent with the study endpoints and objectives.

**Table 2 Clinical Laboratory Tests**

| Hematology                                                                                                                        | Chemistry                                                                                                                                                                         |                                                                                                                                                                                    | Nasal and Oropharyngeal Swabs                                |
|-----------------------------------------------------------------------------------------------------------------------------------|-----------------------------------------------------------------------------------------------------------------------------------------------------------------------------------|------------------------------------------------------------------------------------------------------------------------------------------------------------------------------------|--------------------------------------------------------------|
| RBC
RDW
MCH
MCHC
WBC with differential (% and absolute)
Hemoglobin
Hematocrit
Platelets
aPTT
PT
INR | ALT
Albumin
Alkaline phosphatase
AST
Total bilirubin
Total protein
Creatinine
Blood urea nitrogen
Magnesium
Phosphorus
hsCRP
Ferritin
D-dimer | Potassium
Sodium
Glucose
Chloride
Bicarbonate or CO 2
Calcium
eGFR
Total cholesterol
HDL cholesterol
LDL cholesterol
Triglycerides
LDH | COVID-19
Quantitative Viral Load (research purposes only) |

*Abbreviations: aPTT: activated partial thromboplastin time, ALT: alanine aminotransferase, aPTT: activated partial thromboplastin time, AST: aspartate aminotransferase, CO2: carbon dioxide, CRP: C-reactive protein, eGFR: estimated glomerular filtration rate, HDL: high density lipoprotein, INR: international normalized ratio, LDH: lactate dehydrogenase; LDL: low density lipoprotein, MCH: mean corpuscular hemoglobin, MCHC: mean corpuscular hemoglobin concentration, PT: prothrombin time, RBC: red blood cell, RDW: red cell distribution width, WBC: white blood cell.*

Note: the list of laboratory tests may not be inclusive of all tests conducted throughout the study.

Blood samples may also be assessed for markers of infection, antibody response, and inflammation such as:

- D-dimer, lipocalin, cytokines, IgM/IgG sero-conversion, and Neutralization Assays

Instructions relating to blood and nasal and oropharyngeal swab collection methodologies storage requirements, and shipment requirements will be detailed in the Laboratory Manual.

#### **4.3.10 Telemedicine Visit**

As outlined in the SOA ([Table 1](#)), a healthcare provider (PI or designee) or a centralized telemedicine vendor will conduct a telemedicine study visit. This visit may be used to interview and collect safety information along with other protocol-specified measures of health as needed.

#### **4.3.11 Healthcare Provider Wellness Visit by Telephone**

As outlined in the SOA ([Table 1](#)), a healthcare provider (PI or designee) or a centralized telemedicine vendor will conduct a wellness visit by telephone. This phone call to the patient will be conducted to follow-up on the patient's health status and to ascertain compliance with study procedures.

### **5 STUDY POPULATION**

#### **5.1 Inclusion Criteria**

To be considered for enrollment into this study, each patient must meet **all** of the following Inclusion Criteria:

1. Be male or female,  $\geq 18$  years of age
2. Be willing and able to give informed consent, and provide medical history, and secondary contact information
3. If symptomatic at the time of COVID-19 testing, the extended symptom(s), 8 cardinal plus additional 5 symptom(s) (see [Section 4.3.4.1](#) for reference) must be new or worsening at baseline and must not have been present (see [Section 4.3.4.1](#) for reference) for more than 5 days. Symptomatic patients must be screened and randomized within 48 hours of a positive test.
4. If pre-symptomatic at time of COVID-19 testing, new cardinal symptoms (see [Section 4.3.4.1](#) for reference) must be reported within 7 days of a positive test, and the patient must be screened and randomized within 5 days of them developing symptoms

5. Mild to moderate COVID-19 and self-reported outpatient management indicated by their healthcare provider
6. Able to adhere to the study visit schedule and other protocol requirements
7. Has consistent internet or cellphone access with a data plan, and access to a smartphone, tablet or computer

## 5.2 Exclusion Criteria

Patients who meet **any** of the following Exclusion Criteria will not be enrolled into the study:

1. In the Primary Investigator's judgement, patients likely to require hospitalization for COVID-19
2. Patients who are hospitalized for in-patient treatment or currently being evaluated for potential hospitalization at the time of informed consent for conditions other than COVID-19
3. History of chronic lung disease with chronic hypoxia
4. History of documented cirrhosis or end-stage liver disease
5. Ongoing requirement for oxygen therapy
6. Shortness of breath in resting position
7. Diagnosis of sleep apnea requiring Bilevel Positive Airway Pressure (BIPAP) / Continuous Positive Airway Pressure (CPAP)
8. Female patients who are pregnant, trying to become pregnant or lactating.
9. Concurrent use of any of the following medications:
  - a. Therapy with an immunomodulatory agent within 12 months of study screening
  - b. Systemic antibiotics, antifungals, or antivirals for treatment of active infection within 28 days of study screening
  - c. Systemic immunosuppressive therapy within 3 months of study screening
  - d. Drugs or other compounds that modulate GI motility (including stool softeners, laxatives, or fiber supplements) taken currently, or within 7 days of Study screening. Antacid (H2 blockers and PPIs) and antidiarrheal agents are not prohibited.

Note: Prebiotics and probiotics intake should not be changed during the study (see [Section 6.6](#) for additional details and reference).
10. History of GI surgery (6 months prior to Randomization), including but not limited to bariatric surgery and bowel resection, or history of, or active GI disease(s) that may affect assessment of tolerability, including but not limited to the following:
  - a. Inflammatory bowel disease
  - b. Irritable bowel syndrome
  - c. Autoimmune disease
  - d. GI malignancy
11. Participation in an interventional clinical trial with or use of any investigational agent within 30 days before Randomization

12. Has a clinically significant or uncontrolled concomitant medical condition that would put the patient at risk or jeopardize the objectives of the study in the opinion of the PI
13. Is considered, in the opinion of the PI, to be unlikely for any reason to be able to comply with study procedures
14. Contraindications, sensitivities, or known allergy to the use of the study product or its components

### **5.3 Screen Failures**

Patients who provide informed consent but do not meet the study entry criteria during Screening and consequently are not enrolled in the study are screen failures. Patients may not be re-screened.

### **5.4 Enrollment**

Patients will be randomized in a 1:1 ratio to either SSC + KB109 or SSC alone; see [Section 6](#) for further information on the SP. Consented patients who are withdrawn from the study prior to randomization are deemed screen failures; patients withdrawing after randomization will not be replaced nor re-consented for new participation.

### **5.5 Withdrawal of Patients**

Patients have the right to withdraw from the study at any time for any reason, without giving a reason and without penalty or loss of benefits they are entitled to. The investigator also has the right to withdraw patients from the study if this is in the best interest of the patient.

Patients will be discontinued from the study in the event of any of the following:

- Patient independently withdraws consent from the study (e.g., patient declines further participation in the study)
- PI determines that the patient has developed a concurrent illness, condition, or an AE due to which continued participation in the study and/or SP dosing is considered potentially harmful to the patient and withdrawal is in the best interest of the patient
- Patient discontinues from SP dosing (i.e., due to development of an AE), but continues his/her consent to participate in the study for follow-up only (e.g., for continued collection of AE information)
- Patient failure to comply with study requirements (e.g., failure to properly consume the SP or failure to comply with other protocol-specific assessments) resulting in protocol deviations that make the interpretation of the data not feasible
- Patient becomes pregnant

Patient requires hospitalization due to worsening COVID-19

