### 5.5.1 Handling of Discontinuation of SP and Early Terminations

If the PI discontinues a patient from SP due to development of an AE, the patient wishes to withdraw from the study, or the patient is terminated from the study for any other reason every effort should be made to:

- Complete the Early Termination visit assessments, as directed in the SOA ([Table 1](#))
- Monitor the patient for resolution of any existing AEs, and onset of new AEs for 3 weeks (21 days) after the last dose of SP.

The data should be documented on the appropriate eCRF in the electronic database capture (EDC) system.

If, due to extenuating circumstances, the PI and/or study site team are concerned that the patient may not be able to safely complete all the required visits and assessments the PI should contact the Sponsor's Medical Monitor to discuss whether an early termination visit should occur to enable the return of the SP, and the completion of key end of intake assessments/measures, while ensuring the patient's safety.

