## **6.8 Dose Reductions and Holds**

In the event of significant worsening of COVID-19 symptoms, severe or intolerable GI symptoms, or other attributable AEs, the KB109 dose may be down-titrated to a lower dose, or temporarily interrupted, after consultation with the Medical Monitor.

KB109 down-titration occurs by reducing the dose in a step-wise fashion. Specifically, a patient's dose can be reduced after evaluation by the PI or designee, and in consultation with the Sponsor's medical monitor or designee from 72 g/day (36 g BID) to 36 g/day (18 g BID) followed by 18 g/day (9 g BID) until the attributable AE resolves or adequate tolerability is achieved.

During the Intake Period, and at the discretion of the PI and in consultation with the Medical Monitor, patients who have down-titrated their KB109 dose may attempt to increase their dose. This up-titration can only occur at the next up-titration period. Patients can also remain at the down titrated dose, for the remainder of the intake period.

If the patient requires down-titration below 18 g/day (9 g/dose BID), then consultation with the Medical Monitor and PI or designee must occur, and the patient may be withdrawn from the study.

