### 8.3.2 Full Analysis Set

The Full Analysis Set will include all randomized patients and have both Baseline and at least one post-Baseline endpoint observation during intake period. Patients will be analyzed in the group to which they were randomized.

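### Section 5.5 makes stopping KB109 a discontinuation from the study, so symptom data after exit can be missing in one arm only; this can bias the secondary comparisons, in a direction that cannot be told in advance

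*Protocol*

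**What the plan says.** Section 5.5 introduces its list with "Patients will be discontinued from the study in the event of any of the following". One entry is "Patient discontinues from SP dosing (i.e., due to development of an AE), but continues his/her consent to participate in the study for follow-up only", and the example given for that follow-up is "e.g., for continued collection of AE information". Another entry is non-compliance, including "failure to properly consume the SP or failure to comply with other protocol-specific assessments", but only where the resulting deviations leave the data uninterpretable.

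Section 5.5.1 opens with "If the PI discontinues a patient from SP due to development of an AE" and puts that case in the same sentence as withdrawal and termination from the study. All of them get the Early Termination visit and monitoring of adverse events for 21 days after the last dose. Section 6.8 says of patients who would need less than the lowest dose step that the medical monitor is consulted "and the patient may be withdrawn from the study". Section 6.7, on worsening COVID-19, names hospitalization as the sole ground for removal and cites Section 5.5, which lists several others. Section 4.1 says that all enrolled patients undergo the same procedures.

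On analysis, Section 8.3.2 says "Patients will be analyzed in the group to which they were randomized". Section 3.2.2 defines symptom resolution as a composite score of 0 or 1 held through the Follow-up Period, and sets oxygen saturation endpoints on Days 14 and 35. Section 8.4.3 takes the end-of-intake score from Days 12 to 14 and reports a group difference with a 95% confidence interval.

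**The concern.** Stopping the product and leaving the study are different events, and Section 5.5 merges them. A site cannot tell whether a patient who stops KB109 but still consents should go on with the diary. If the site follows the list and Section 5.5.1, scheduled symptom collection ends at the Early Termination visit.

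The supportive self-care (SSC) arm has no product, so no SSC patient can leave by this route. The exit is also foreseeable: the dose reaches 72 g/day from Day 5 (Table 3), and Section 7.3.1 expects gastrointestinal intolerance at higher amounts. The data at risk are those needed for the end-of-intake scores, time to resolution, Day 14 and Day 35 oxygen saturation, and utilization. Analysis as randomized keeps these patients in their group but supplies no values after exit. An analysis plan can set a censoring or imputation rule; it cannot recover diary entries that were never collected.

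**Working it through.** **The plan's own figures.** With 15% attrition (Section 8.1), 350 × 0.85 = 297.5, or 148.75 per group, stated as 296 and 148. Likewise 400 × 0.85 = 340, or 170 per group, as stated. All eight rows of Table 4 reproduce with exact (Clopper-Pearson) intervals; for example 15/148 gives 5.8% to 16.2%, half-width 5.2%. These figures are sound and this point does not change them. The 15% is not split by arm or cause, and the protocol gives no effect size, standard deviation or rate of stopping KB109. What follows therefore rests on assumptions.

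**What remains after exit.** The Early Termination column of Table 1 marks temperature and oxygen saturation, the symptom check, global impression, utilization and bedrest, once. It marks no quality-of-life questions, swabs or blood. For a last dose on Days 3 to 10, monitoring for 21 days ends on Days 24 to 31, against Day 35 in the SSC arm. Section 7.1 collects adverse events to the end of follow-up, so these two rules also need aligning.

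**Change score.** If a share f of the KB109 arm leaves and would have scored D points worse at end of intake than those who stay, the observed-case difference (KB109 minus SSC) shifts by -f × D.
- f = 5%, D = 1: -0.05 points. f = 20%, D = 4: -0.8 points. Both favour KB109.
- D = 0: no shift.
- D = -2 (leavers better after stopping): +0.1 points at f = 5% and +0.4 at f = 20%, against KB109.

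**Time to resolution.** Assume two arms identical in truth, a constant resolution hazard of 0.055/day, and KB109 stoppers leaving on Days 3 to 10. HR is the stoppers' resolution hazard relative to the other patients. By Day 35 the others have resolved in 1 - exp(-0.055 × 35) = 85.4%.

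Take 15% stoppers with HR 0.5:
- Stoppers resolve in 1 - exp(-0.0275 × 35) = 61.8%.
- True rate with full follow-up: 0.85 × 85.4 + 0.15 × 61.8 = 81.9%.
- Censored at exit, simulated Kaplan-Meier gives 85.0%, a shift of +3.1 points.
- Counted as unresolved unless resolved before exit (mean exit Day 6.5): 1 - exp(-0.0275 × 6.5) = 16.4%, so 0.85 × 85.4 + 0.15 × 16.4 = 75.1%, a shift of -6.8 points.

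| KB109 patients stopping | HR | Handling of leavers | Shift in KB109 Day 35 resolution (points) |
|---|---|---|---|
| 15% | 0.5 | censored at exit | +3.1 |
| 15% | 0.3 | censored at exit | +5.6 |
| 20% | 0.3 | censored at exit | +7.4 |
| 5-20% | 1.0 | censored at exit | 0 |
| 5-20% | 1.5 | censored at exit | -0.3 to -1.3 |
| 15% | 0.5 | counted as unresolved | -6.8 |
| 20% | 0.3 | counted as unresolved | -6.7 |

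Medians behave the same way. With an assumed median of 14 days and 20% leavers, full follow-up against censoring gives 15.8 against 14.7 days at HR 0.5, 14.1 against 14.1 at HR 1, and 12.8 against 13.4 at HR 1.5. With full follow-up of stoppers the shift is zero in every scenario.

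**The case against.** A reader might infer that the rule biases the trial toward KB109. The documents do not support that. Nothing in them says that patients who stop KB109 recover more slowly from COVID-19. Section 2.3 calls the gastrointestinal effects quickly reversible, and the 8-symptom composite contains no gastrointestinal item, although the 13-symptom composite has two. Section 8.4.3 names Kaplan-Meier but fixes no censoring rule, and further details are left to an analysis plan that is not shown. As the table shows, the sign turns on both choices. This objection stands.

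A reader might also infer that every related exit belongs to KB109 alone. It does not. The bullet on illness or adverse events covers participation in the study as well as dosing, so it reaches SSC patients. The non-compliance bullet covers missed assessments in either arm and carries the interpretability condition. Withdrawal under Section 6.8 is discretionary. This also stands.

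Nor are outcomes lost altogether. Scores before exit and one Early Termination reading remain, and the change-score model uses the Day 2-4 and Day 5-11 visits. Adverse event information is only an example of the retained follow-up. Hospital admissions are largely caught as serious adverse events, which Section 7.4.3 collects to the end of follow-up. The primary endpoint, product-related adverse events, is still collected after the product is stopped.

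These replies narrow the scope and remove the claimed direction. They do not resolve the contradictory bullet or restore scheduled symptom collection after an exit that only one arm can take.

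**Conclusion.** The point holds in limited form. Section 5.5 treats stopping KB109 as leaving the study, contradicts itself within one bullet, and does not fit with Section 6.7. Section 5.5.1 provides no continued diary, wellness calls or Day 14 and Day 35 visits. The result is possible one-armed, treatment-related missing data in the secondary symptom, oxygen saturation and utilization comparisons.

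Under the assumptions shown, the shift in Day 35 resolution runs from about +7 points (slow recovery, censoring at exit) through zero to about -7 points (slow recovery, counted as unresolved). The shift in the change score runs from -0.8 to +0.4 points. Stopping rates, hazard ratios, score differences and the handling of leavers are all assumptions, so neither a direction nor a single size should be quoted. The primary safety endpoint and Table 4 are largely untouched. This should be fixed, because data not collected cannot be recovered later, but it does not undermine the primary objective.

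**What to change.** Reconcile Sections 5.5, 5.5.1, 6.7 and 6.8 so that discontinuation of study product and discontinuation from the study are separate events.

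- In Section 5.5, take stopping the product on its own, and not taking the product on its own, off the list of reasons for leaving the study.
- In Sections 5.5.1 and 6.8, state that a patient who stops the product and still consents keeps the scheduled diary, wellness calls and Day 14 and Day 35 visits, as in the SSC arm.
- State in Section 8.3.2 that data collected after the product is stopped are analysed in the randomized group.
- Align the removal sentence in Section 6.7 with the revised list, and the 21-day monitoring window in Section 5.5.1 with Section 7.1.

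The rules on when the product is stopped, interrupted or reduced are left as they are.

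The cost is a wording amendment with the IRB review that Section 9.2.1 requires. No new procedure and no extra enrollment are needed. If 5% to 20% of 175 to 200 KB109 patients stop (an assumption), about 9 to 40 patients would continue assessments that are already scheduled.

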### 3.2.2 Secondary Endpoints

The secondary endpoints are as follows:

- Time to resolution of overall 13 COVID-19 related symptoms which is defined as from Day 1 until the day at which the overall composite score of 13 COVID-19 related symptoms becomes 0 or 1 and remains at 0 or 1 for the rest of the Intake Period and for the Follow-up Period. Overall composite score of 13 COVID-19 related symptoms is the sum of 13 COVID-19 related symptom scores (i.e., cough, chills/repeated shaking with chills, muscle pain, fever, headache, anosmia/ageusia, shortness of breath, sore throat, gastrointestinal disturbance/symptoms, diarrhea, fatigue, nasal congestion, and chest tightness (CDC 2020). Each COVID-19 symptom will be recorded by patients on a scale of 0: Absent, 1: Mild, 2: Moderately severe, 3: Very severe. The overall composite score ranges from 0 (no symptoms) to 39 (very severe)
- Time to resolution of overall 8 cardinal COVID-19 related symptoms which is defined as from Day 1 until the day at which the overall composite score of 8 cardinal COVID-19 related symptoms becomes 0 or 1 and remains at 0 or 1 for the rest of the Intake Period and for the Follow-up Period. Overall composite score of 8 cardinal COVID-19 related symptoms is the sum of 8 cardinal COVID-19 related symptom scores (i.e., cough, chills/repeated shaking with chills, muscle pain, fever, headache, anosmia/ageusia, shortness of breath, and sore throat)
- Proportion of patients with reduction from Baseline (symptom present at Baseline) in each of 13 individual COVID-19 related symptom at EOI and Follow-up
- Proportion of patients with symptom becomes absent (symptom present at Baseline) at EOI and Follow-up for each of 13 individual COVID-19 related symptom
- Change from Baseline to EOI in overall composite score of 13 COVID-19 related symptoms
- Change from Baseline to EOI in overall composite score of 8 cardinal COVID-19 related symptoms
- Time to resolution of fever (defined as from Day 1 until the day at which a patient's daily maximum temperature achieves and remains below 100.4 °F for the rest of the Intake Period and for the Follow-up Period without an antipyretic medication)
- Proportion of patients with oxygen saturation <95% on Day 14 and Day 35

- Proportion of patients with oxygen saturation <98% on Day 14 and Day 35
- Measures collected from the Healthcare Provider Wellness Visits

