- Proportion of patients experiencing hospital admissions during the Intake Period and Follow-up Period (all cause, and COVID-19-related)
- Healthcare Utilizations during the Intake Period and Follow-up Period

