## 6.7 Self-supportive Care

Patients with COVID-19 should follow the steps as instructed by their healthcare provider (consistent with guidance from the CDC, local ordinances or practices) to care for themselves and to help protect other people in the home and community from potentially getting sick ([CDC 2020](#)).

In order to manage the symptoms associated with COVID-19, over-the-counter cough, cold, and anti-pyretic medications can be used as necessary by patients in accordance with their respective drug facts label or as instructed by their healthcare provider.

The brand name, generic name, dose, and time must be recorded for every usage occasion.

Since this is an out-patient based study, in the event of significant worsening of COVID-19-related symptoms or two sequential pulse oximetry readings of <94%, patients will be instructed to seek medical attention immediately with their treating provider or go to the emergency room. If the PI or study staff are contacted due to significant clinical worsening of COVID-19 symptoms, the patient will be triaged appropriately to the emergency room or to the outpatient treating provider per clinical judgement. The patient will be removed from the study only if hospitalized (refer to [Section 5.5](#)).

Patients will be provided with information consistent with CDC guidance regarding emergency warning signs for COVID-19 ([CDC 2020](#)) instructing them to seek medical attention immediately, if any of the following occur:

- Trouble breathing
- Persistent pain or pressure in the chest
- New confusion or inability to arouse
- Bluish lips or face

A medical provider must be contacted for any other symptoms that are severe or concerning to the patient. Patients will be instructed to call 911 if they have a medical emergency and be instructed to notify the operator that they have, or think they might have, COVID-19.

Patients will be instructed to put on a cloth face covering before medical help arrives.

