#### Time to resolution of overall 13 COVID-19 related symptoms and the 8 cardinal COVID-19 related symptoms

The Kaplan-Meier method will be used to estimate median time to resolution and resolution rate specific to each group. Kaplan-Meier graphs will be generated; quartiles and point probabilities will be calculated. Interval estimates will be calculated using 95% point-wise CIs.

Proportion of patients with reduction from Baseline (symptom present at Baseline) and proportion of patients with symptom becomes absent (symptom present at Baseline) at EOI and Follow-up for each of 13 individual COVID-19 related symptom will be summarized by group using frequencies and percentages.

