#### Time to resolution of fever

The Kaplan-Meier method will be used to estimate median time to resolution of fever and resolution rate specific to each group. Kaplan-Meier graphs will be generated; quartiles and point probabilities will be calculated. Interval estimates will be calculated using 95% point-wise CIs.

Proportion of patients with oxygen saturation <95% (or <98%) on Day 14 and Day 35, and proportion of patients experiencing hospital admissions during the Intake Period and Follow-up Period will be summarized by group using frequencies and percentages.

Measures collected from the Healthcare Provider Wellness Visits and Healthcare Utilizations during the Intake Period and Follow-up Period will be summarized by group based on the Safety Analysis Set using the following descriptive statistics: sample size, mean, standard deviation, median, minimum value, and maximum value or using frequencies and percentages.

Further details of the model specification, assumptions, and SAS implementation codes will be provided in the SAP.

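### Removing patients from the study on COVID-19 hospitalization ends their symptom follow-up for a reason tied to the outcome, so sustained resolution to Day 35 cannot be observed for them

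*Protocol*

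**What the plan says.** Protocol Section 5.5 (Withdrawal of Patients) gives the events on which a patient is discontinued from the study. One is "Patient requires hospitalization due to worsening COVID-19". Section 6.7, on worsening symptoms and low oximetry readings, refers back to that rule: "The patient will be removed from the study only if hospitalized".

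Section 5.5.1 sets out what is still collected after a termination for any reason. The site should make every effort to "Complete the Early Termination visit assessments, as directed in the SOA", and to monitor adverse events for 21 days after the last dose of study product. Patients on supportive self-care alone take no study product, so that window has no starting point in their arm. Section 5.5.1 names no continuing symptom, temperature or saturation schedule.

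Section 3.2.2 defines resolution of the 13-symptom and the 8-symptom composite as the day the score "becomes 0 or 1 and remains at 0 or 1 for the rest of the Intake Period and for the Follow-up Period". Fever resolution carries the same requirement to the end of follow-up. Section 8.4.3 names one estimator for the composites, "The Kaplan-Meier method will be used to estimate median time to resolution and resolution rate specific to each group", and the same one for fever, "The Kaplan-Meier method will be used to estimate median time to resolution of fever and resolution rate specific to each group". It gives no rule for a patient removed on admission and leaves model details and assumptions to the SAP.

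**The concern.** Admission for worsening COVID-19 is not random loss. It marks a patient whose disease is moving away from resolution. Removal at that moment makes the missing data depend directly on the outcome being measured.

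Two things follow. First, because resolution must be sustained through Day 35, the endpoint cannot be determined from data that stop at an Early Termination visit. A SAP can choose an estimator, but it cannot recover symptom scores that were never collected. Second, if these patients are censored at removal, Kaplan-Meier assumes that they would have recovered like patients still at home. That overstates recovery, and the overstatement is larger in the arm with more admissions. The natural-history aim in the study title also loses part of its severe tail.

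**Working it through.** **The plan's own figures.** The protocol states no admission rate and no time to resolution, so there is no figure on this point to reproduce. The sample-size figures only give patient counts. With 15% attrition, 350 × 0.85 = 297.5 (148.75 per group; the protocol gives 296, or 148 per group) and 400 × 0.85 = 340 (170 per group, as stated).

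**Inputs.**
- From the protocol: 175 to 200 randomized per group, a 14-day Intake Period, follow-up to Day 35.
- Assumed: median time to resolution m = 14, 21 or 28 days; share admitted for COVID-19 h = 1%, 2%, 5% or 10% (about 2 to 20 patients per arm); admissions only on Days 1-14; no other dropout; admitted patients not resolved by Day 35. The last makes the result an upper bound.

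**Formulas (daily steps).**
- Daily resolution hazard: λ = 1 − 0.5^(1/m).
- Censoring at removal: the Kaplan-Meier share resolved at Day 35 is 1 − (1 − λ)^35 = 1 − 0.5^(35/m). It does not depend on h.
- Keeping admitted patients as not resolved: let q be the daily admission hazard on Days 1-14 among those not yet resolved, and g = (1 − λ)(1 − q). Choose q so that (1 − λ) q (1 − g^14)/(1 − g) = h. The share resolved at Day 35 is then λ(1 − g^14)/(1 − g) + g^14 [1 − (1 − λ)^21].

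**One case in full (m = 14, h = 10%).** λ = 0.0483. Censoring gives 1 − 0.5^2.5 = 82.3%. Solving for q gives 0.0108. The share resolved by Day 14 is 0.4704, and g^14 = 0.4296 are still at home and unresolved. Of these, 0.6464 resolve on Days 15-35, adding 0.2777. The total is 0.4704 + 0.2777 = 74.8%, so censoring overstates by 7.5 points.

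**All cases: share resolved at Day 35.**

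| Assumed median | Censored at removal | 1% admitted | 2% | 5% | 10% | Overstatement (points), 1% / 2% / 5% / 10% |
|---|---|---|---|---|---|---|
| 14 days | 82.3% | 81.6% | 80.8% | 78.6% | 74.8% | 0.7 / 1.5 / 3.7 / 7.5 |
| 21 days | 68.5% | 67.9% | 67.3% | 65.5% | 62.5% | 0.6 / 1.2 / 3.0 / 6.0 |
| 28 days | 58.0% | 57.5% | 57.0% | 55.5% | 53.0% | 0.5 / 1.0 / 2.5 / 5.0 |

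The median lengthens by 1 day at 1-2% admitted and by 2 to 4 days at 10% (14 to 16, 21 to 24, 28 to 32). The model counts whole days, so the 1-day shift at low rates is partly rounding.

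**Unequal arms.** Give both arms the same resolution hazard, with 2% admitted in one and 8% in the other. Censoring at removal shows no difference between arms, by construction. The share actually resolved at Day 35 differs by 4.5 points (median 14 days) or 3.6 points (median 21 days).

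**The case against.** The strongest objection is that the protocol never says these patients are censored at removal. A reader might infer it from Kaplan-Meier being the only estimator named, but the text does not support that. Section 8.4.3 leaves details to the SAP, which is not at hand. Kaplan-Meier also allows an admitted patient to be held as unresolved to Day 35 from the admission date alone. This stands, so the bias above is conditional.

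A reader might also infer that admissions are lost or that an arm difference in severe outcomes is hidden. Neither follows:
- Admission, all-cause and COVID-19-related, is a secondary endpoint. The Synopsis places it on the Safety Analysis Set, which contains all randomized patients.
- Hospitalization is a serious adverse event criterion (Section 7.4.1), reported to the end of follow-up (Section 7.4.3). Section 7.4.4 takes admission and discharge as its onset and resolution dates.
- The daily utilization diary stops for a removed patient. But the Early Termination column of Table 1 includes the utilization questions and one record of symptoms, temperature and saturation, so the triggering admission can be recorded.

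Nor is the composite-score analysis simply empty for these patients. Its model uses three intake windows, and a patient removed late still contributes the earlier ones. Only the later windows are missing.

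On size, eligibility excludes patients judged likely to need hospitalization, on oxygen, or short of breath at rest, which points to the low end of the range. There the error is small beside sampling error: with 175 per arm and 80% resolved, the 95% half-width is 1.96 × √(0.8 × 0.2/175) = 5.9 points. The endpoints are secondary and summarized with point-wise intervals, and the amendment history says that no hypothesis is tested. The same history explains the removal by the outpatient setting. That justifies ending home-based procedures. It does not explain why outcomes could not be collected by telephone or from records.

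**Conclusion.** The point holds as a data-collection defect with a conditional analysis consequence. What the protocol fixes badly is that removal on COVID-19 admission ends scheduled symptom, temperature and saturation reporting for a reason tied to the outcome. The sustained resolution endpoints then cannot be observed for these patients, and no later analysis document can restore them. The safety window after removal also has no defined start in the supportive self-care arm.

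If the analysis censors at removal, the Day 35 resolved share is overstated by about 0.5 to 1.5 points at 1-2% admitted and 5 to 7.5 points at 10%, more so in the arm with more admissions. This rests on an assumed 14- to 28-day median, admissions confined to Days 1-14, and no admitted patient resolving by Day 35. The real admission rate is not in the protocol. The primary endpoint does not use these analyses and is unaffected. The point should be fixed because the change is cheap, but it does not put the trial's main result at risk.

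**What to change.** In Sections 5.5, 5.5.1 and 6.7, separate leaving the outpatient procedures from leaving the study. For a patient admitted with COVID-19 who still consents, continue outcome collection to Day 35, counted from Day 1 in both arms. Take the symptom score at the telephone and telemedicine contacts already planned (Days 3, 7, 10, 14, 21, 28 and 35) when the patient is able. Take vital status and admission and discharge dates from the serious adverse event records. Section 5.5 already mentions patients who consent to follow-up only, so the idea is not new to the plan.

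In Section 8.4.3, state that COVID-19 admission or death before resolution is not a censoring event at removal. Either keep a patient with no later symptom data as not resolved to Day 35, or handle the event as a competing event and report cumulative incidence.

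The cost is protocol wording, a few extra telephone contacts and slightly longer reported medians. Decisions about study product and clinical care are untouched.
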